### Sample Size Determination

The primary outcome of the study is to measure the proportion of participant deaths from any cause within the first 7 days after randomization. We anticipate that the mitigation of inflammation and edema will lead to fewer deaths in the MW189 arm during the acute phase. However, with an abundance of caution, we assume the placebo arm will have a similar number of deaths as compared to the MW189 arm. Therefore, we conducted a noninferiority power analysis using previously collected data from the Minimally Invasive Surgery Plus Alteplase for Intracerebral Hemorrhage Evacuation (MISTIE) III [27] and Antihypertensive Treatment of Acute Cerebral Hemorrhage II (ATACH-2) trials [28] to approximate the safety events that will be seen in the trial.

Considering a power of 80% and a one-sided 90% confidence interval, to test the null hypothesis of noninferiority with a tolerance limit of 12% and assuming a “worst-case” safety assumption of 10% rate of death in each arm, the sample size per group was estimated to be 57. We assume a low overall withdrawal rate in the first 7 days, and therefore 120 participants (60 per group) are required to evaluate the safety of MW189. This number also meets the estimated sample size for an 80% power and two-sided *α* to detect various assumed differences in PHE volume and maximum observed effect (*E*_max_) values in the interleukin-10 plasma cytokine response between treatment arms.

### Statistical Analyses

The intention-to-treat analysis set (all randomized participants) will be used for efficacy analysis. All participants who receive any study treatment will be included in the safety analyses. Continuous variables of normal distribution will be expressed as mean ± standard deviation, whereas continuous variables of nonnormal distribution will be expressed as median and interquartile range. Categorical variables will be represented as frequencies and percentages. We anticipate no missing data for the primary outcome, as all-cause mortality within 7 days of treatment initiation is verifiable.

The primary outcome will involve an estimate of the difference in the proportion of all-cause mortality within 7 days of treatment initiation using a 90% one-sided confidence interval on the upper bound of this difference. The null hypothesis will be rejected if this confidence interval is less than 10%. In addition, we will also estimate the treatment difference in the proportion of 7-day all-cause mortality using a multivariable logistic regression model. This model will consider age, sex, race and ethnicity, ICH volume at stability, Glasgow Coma Scale (GCS) score, presence of IVH, withdrawal of life-sustaining therapy, and ICH location (deep versus lobar). This trial encompasses infratentorial ICH, which comprises brainstem ICH classified as deep location and cerebellar ICH classified as lobar location. Age, sex, and race and ethnicity data are collected at the screening visit. The GCS score is measured at baseline. Presence of IVH and ICH location are determined based on the diagnostic CT scan. The ICH volume assessed on the stability CT scan determines the need for additional imaging to establish hematoma at 6-h intervals until the end of the enrollment period. Withdrawal of life-sustaining therapy information is collected at any time during the study period. The schedule of activities is detailed in Table 2.

**Table 2 Tab2:** Schedule of activities

Activities	Screening/enrollment first dose	Treatment				Follow-up		
Day	1	2	3	4	5	30 (clinic)	90 (phone)	180 (clinic)
Time frame	First dose within 24 h of ICH onset							
Pre-randomization								
Diagnostic CT	X							
CTA/MRI to rule out underlying lesion	X							
Inclusion/exclusion criteria review	X							
Consent by participant or legally authorized representative	X							
MRI to rule out underlying lesion	X							
Stability CT	X							
Pregnancy test	X							
Demographics	X							
Medical history and admission information	X							
Concomitant medications review	X							
At randomization								
Vital signs	X							
Glasgow Coma Scale	X							
Baseline (premorbid) modified Rankin Scale (caregiver interview)	X							
Post randomization								
Research MRI					X			
Usual care clinical CT		X	X	X				
Research CT					X			
Therapy intensity level	X	X	X	X	X			
National Institutes of Health Stroke Scale	X	X	X	X	X	X		X
Glasgow Outcome Scale-Extended						X	X	X
Glasgow Coma Scale	X	X	X	X	X	X		X
Montreal Cognitive Assessment					X	X		X
Stroke Impact Scale-16					X	X		X
Barthel Index	X				X	X	X	X
Modified Rankin Scale						X	X	X
EQ-5D						X	X	X
Center for Epidemiological Studies–Depression						X	X	X
Concomitant medications review		X	X	X	X	X	X	X
Plasma biomarkers	X		X		X			
Cerebrospinal fluid biomarkers	X		X		X			
Pharmacokinetic blood samples	X	X	X		X			
Dosing	X	X	X	X	X			
Adverse events assessment	X	X	X	X	X	SAE/MEOI	SAE	SAE

CT, computed tomography; CTA, computed tomography angiography; ICH, intracerebral hemorrhage; MEOI, medical event of interest; MRI, magnetic resonance imaging; SAE, serious adverse events

Secondary and exploratory safety outcomes will be analyzed using appropriate linear or logistic regression models and will account for treatment group, age, GCS score, presence of IVH, ICH volumes, the timing of drug administration, and hematoma location. No imputation of missing safety end points will be used. Instead, sensitivity analyses will be performed, whereby participants with missing secondary safety data will be assumed to have had a safety event and then not to have had a safety event. The analyses will account for the variability in dosing and treatment duration, which can range from 2 to 10 doses depending on the date of discharge. This variability will be addressed through various approaches, such as categorizing participants into dose groups, treating the number of doses as a continuous variable, and calculating area under the curve that considers the dose and duration of the doses given. The point estimate of the proportion of total safety events and corresponding two-sided 95% confidence intervals will be calculated under both extreme scenarios to provide estimates of uncertainty in the presence of these missing data. SAS, STATA 17, and/or R software will be used for statistical analysis. Statistical significance will be set at *p* < 0.05.

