### Randomization and Blinding

Randomization will be performed by a computer-generated randomization schedule that will assign participants 1:1 to either MW189 or placebo. The allocation sequence will be created and stored in a protected electronic data capture system. All providers and nurses participating in the treatment plan will be excluded from data and outcome analyses. The observers who assess the clinical outcomes will be blinded to the randomization results. A safety review will be performed in a blinded manner unless the data warrants unblinding because of the nature of any safety concerns. When unblinding is required, requests will be directly forwarded to the study’s unblinded statistician by the site investigator. To further maintain blinding during study drug administration, the IV equipment will be covered. Once the study drug is diluted, it must be stored at ambient temperature and protected from light until administration.

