### Study Outcomes

The primary study outcome is the proportion of deaths from all causes during the first 7 days post randomization. Secondary outcomes include all-cause mortality at 30 days, hematoma expansion and recurrent ICH, brain infection, standard pharmacokinetic parameters (time to maximum plasma concentration [*T*_max_], *C*_max_, area under the curve, half-life [*t*_1/2_], clearance [CL], volume of distribution during terminal phase [*V*_z_], apparent terminal elimination rate constant [λ_z_]) determined at different times after MW189 administration, radiographic measures of edema during treatment and at the end of treatment for days 1–5, and measures of plasma and cerebrospinal fluid inflammatory and neuronal injury biomarkers during treatment and at the end of treatment for days 1–5. We will use a semiautomated threshold approach (range 44–100 Hounsfield units) to determine hematoma volume. Significant hematoma expansion will be defined as an increase between baseline and any follow-up CT scan of > 6 mL or > 33%. IVH volume will not be included in hematoma expansion. Recurrent ICH refers to the emergence of a new ICH following an initial episode of spontaneous ICH. It is subsequent spontaneous bleeding in the brain distinct from the initial event, typically occurring after a time frame of around 30 days or more. This is different from ICH expansion, which involves the enlargement of the initial bleed without the occurrence of a completely new bleeding event. Brain infection refers to infection present within the brain tissue and is evaluated based on the clinical symptoms, laboratory test results, and imaging findings. Radiographic measures of edema refer to the quantitative assessment of PHE and will be analyzed via both CT and magnetic resonance imaging (MRI) scans using semiautomated volumetrics with OsiriX software to compare the volume of edema between the two treatment groups. The primary imaging outcomes are absolute PHE and relative PHE and edema extension distance measured on brain CT scans performed at admission and at day 5 of the infusion. PHE measurements on MRI will be performed on the subset with MRI at baseline and at the end of the study. Group differences in edema volumes will be compared.

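### The noninferiority decision on 7-day mortality uses an unadjusted risk difference; adjusting it for three prognostic factors measured before dosing would be a cheap, modest efficiency gain

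*Protocol article*

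**What the plan says.** The Statistical Analyses section of the protocol article attaches the decision to one statistic. It begins: "The primary outcome will involve an estimate of the difference in the proportion of all-cause mortality within 7 days of treatment initiation". A one-sided 90% upper confidence limit for that difference is compared with a margin of 10%. No covariate is named for this analysis.

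Adjustment follows as a second analysis: "In addition, we will also estimate the treatment difference in the proportion of 7-day all-cause mortality using a multivariable logistic regression model". Its covariates are age, sex, race and ethnicity, ICH volume at stability, GCS score, IVH, withdrawal of life-sustaining therapy and ICH location. No decision rule is attached to it.

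Three of these covariates are clearly known before the first dose:

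- Age is recorded at screening.
- On GCS the section says: "The GCS score is measured at baseline". Table 2 lists it at randomization.
- ICH volume on the diagnostic and stability scans is an eligibility criterion in Table 1.

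Age, GCS and ICH volume also appear as covariates in the models for secondary and exploratory safety outcomes. Withdrawal of life-sustaining therapy is different: it is recorded at any time during the study.

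The Sample Size Determination section starts from "Considering a power of 80% and a one-sided 90% confidence interval", a 12% tolerance limit and 10% deaths in each arm. It arrives at 57 per group, and 60 are to be enrolled.

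**The concern.** The plan treats age, GCS and hematoma volume as prognostic in its other models and leaves them out of the one analysis that decides the trial. Eligible volumes run from 10 to 60 mL, so severity at entry can vary a good deal. The assumptions imply only about 12 deaths (0.10 × 120), and the result is sensitive to how a few of them fall. Adjusting for pre-dose severity removes some of that noise. The adjusted risk difference estimates the same quantity against the same margin, using data already held. At stake is some precision in the deciding estimate, not its validity.

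**Working it through.** **Inputs from the article.** 10% deaths per arm, true difference 0, one-sided alpha 0.10 (z = 1.2816), 80% power (z = 0.8416), 60 per arm. The margin is 12% in Sample Size Determination and 10% in Statistical Analyses.

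**Input not in the article.** The strength of the link between covariates and death. Every gain below therefore rests on an assumption, shown as a range.

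**1. The plan's own figure.** With the unadjusted variance, n per group = 2 × 0.10 × 0.90 × (1.2816 + 0.8416)² / 0.12² = 56.35, rounded up to 57. This reproduces the stated number and confirms that the trial was sized for a crude comparison.

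**2. Crude power at 60 per arm.** SE = √(2 × 0.10 × 0.90 / 60) = 0.0548.

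- 12% limit: Φ(0.12/0.0548 − 1.2816) = 81.8% (exact binomial 82.1%).
- 10% limit: Φ(0.10/0.0548 − 1.2816) = 70.7% (exact binomial 71.9%).

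**3. Sensitivity to a few deaths.** Crude Wald upper limits with 12 deaths in total:

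| Deaths, MW189 vs placebo | Upper limit |
|---|---|
| 6 vs 6 | 7.0% |
| 7 vs 5 | 10.3% |
| 8 vs 4 | 13.6% |

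**4. Gain by formula.** If covariates explain a share R² of the outcome variance, power = Φ(margin / √(0.003 × (1 − R²)) − 1.2816), where 0.003 = 0.18/60.

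| Assumed R² | 12% limit | 10% limit |
|---|---|---|
| 0.05 | 83.3% (+1.5) | 72.3% (+1.6) |
| 0.10 | 84.8% (+3.0) | 74.0% (+3.3) |
| 0.25 | 89.4% (+7.6) | 79.6% (+8.9) |

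The formula takes R² as fully recovered and charges nothing for estimating coefficients from about 12 deaths. It is an upper guide.

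**5. Gain by simulation.** 60 per arm, 10% deaths, three prognostic covariates, 3,000 trials per cell; crude Wald limit against a linear model with HC3 standard errors:

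| AUC (R²) | 12% limit, crude → adjusted | 10% limit, crude → adjusted |
|---|---|---|
| 0.71 (0.06) | 82.7% → 82.7% | 72.4% → 71.8% |
| 0.79 (0.13) | 81.2% → 82.4% | 70.6% → 71.1% |
| 0.85 (0.23) | 82.1% → 85.4% | 73.2% → 75.7% |
| 0.90 (0.34) | 82.8% → 86.4% | 70.6% → 75.0% |

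Type I error at the margin was 9.3–10.1% for the linear model and 10.1–11.0% for the crude limit. A further simulation with HC2 and HC3 errors gave about 0 to +1 point at weak prognosis, +2 to +3 at moderate and +3.5 to +4.5 at strong, with type I error of about 9.5–10.8% against 10.1–11.4% crude.

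**6. Logistic standardization.** In the simulation of step 5 at the 12% limit, a standardized risk difference from a logistic model gained about 1, 3, 6 and 9 points across the four rows. Its type I error was 10.7–11.9%, so part of that gain comes from a limit that is slightly too narrow.

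**7. Fewer deaths.** At 5% deaths per arm, SE = √(2 × 0.05 × 0.95 / 60) = 0.0398. Crude power is about 96% (12% limit) and 89% (10% limit), and linear adjustment changes it by about −1 to +1.5 points.

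**The case against.** The strongest reply is that nothing here is wrong. An unadjusted risk difference is a valid primary analysis, it matches the sample size calculation, and it delivers the stated 80% power at the 12% limit. That stands, and it fixes the weight of the point.

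The article also calls 10% mortality a worst case. With fewer deaths, crude power is already high and adjustment does almost nothing. Eligibility rules that limit volume and exclude unstable hematomas may narrow the prognostic spread further. These arguments stand too, and they are why the range starts at zero.

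Three stronger readings are tempting, and the documents do not support them:

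- **That the plan gives up 3 to 9 points of power.** That range needs an assumed R² of about 0.10 to 0.25 and a formula that ignores estimation cost. The article gives no R² or AUC, and a method that holds its error rate gains less.
- **That the additional model yields only an odds ratio, which cannot be compared with the margin.** The article says that model estimates a difference in proportion, and how it does so may be left to the analysis plan.
- **That randomization is unprotected against imbalance.** The article says: "Randomization will be performed by a computer-generated randomization schedule that will assign participants 1:1 to either MW189 or placebo". It names no stratification factor, but a condensed article's silence does not show there is none. Chance imbalance is in any case imprecision that the confidence interval already covers, not bias.

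**Conclusion.** The point holds as an efficiency improvement. The deciding analysis leaves out three pre-dose covariates that the plan itself treats as prognostic. Adjusting for them with a linear model and robust standard errors gains roughly 0 to 4 points of power. This assumes 10% deaths per arm, 60 per arm, three covariates and prognostic strength between AUC about 0.7 and 0.86. At 5% deaths the change is about −1 to +1.5 points. The prognostic strength is an assumption throughout.

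The conflict between the 12% and 10% margins is a separate matter and a larger one: it costs 81.8 − 70.7 = 11.1 points with no assumption about covariates. Adjustment does not resolve it.

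**What to change.** Before unblinding, prespecify the deciding estimate as the treatment coefficient from a linear model for 7-day death with robust standard errors (HC2 or HC3, the choice fixed in advance), adjusted for age, GCS score and ICH volume at stability only. Compare its one-sided 90% upper limit with the single margin, once the 12% and 10% figures have been reconciled. Report the crude difference and its limit as a supporting analysis.

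The additional logistic model should not simply be promoted to this role. It has at least eight covariates for about 12 deaths, and it includes withdrawal of life-sustaining therapy, which can occur after randomization and so must stay out of the deciding model. A standardized logistic estimate is also not advised here, because its type I error ran at about 11–12%.

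The cost is wording in the analysis plan, with no new data, visits or participants. The downside is that the gain may be negligible, or very slightly negative, if the covariates are weakly prognostic or deaths are few. The covariate set must stay at two or three terms.

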## Abstract

Patients with acute spontaneous intracerebral hemorrhage (ICH) develop secondary neuroinflammation and cerebral edema that can further damage the brain and lead to increased risk of neurologic complications. Preclinical studies in animal models of acute brain injury have shown that a novel small-molecule drug candidate, MW01-6-189WH (MW189), decreases neuroinflammation and cerebral edema and improves functional outcomes. MW189 was also safe and well tolerated in phase 1 studies in healthy adults. The proof-of-concept phase 2a Biomarker and Edema Attenuation in IntraCerebral Hemorrhage (BEACH) clinical trial is a first-in-patient, multicenter, randomized, double-blind, placebo-controlled trial. It is designed to determine the safety and tolerability of MW189 in patients with acute ICH, identify trends in potential mitigation of neuroinflammation and cerebral edema, and assess effects on functional outcomes. A total of 120 participants with nontraumatic ICH will be randomly assigned 1:1 to receive intravenous MW189 (0.25 mg/kg) or placebo (saline) within 24 h of symptom onset and every 12 h for up to 5 days or until hospital discharge. The 120-participant sample size (60 per group) will allow testing of the null hypothesis of noninferiority with a tolerance limit of 12% and assuming a “worst-case” safety assumption of 10% rate of death in each arm with 10% significance and 80% power. The primary outcome is all-cause mortality at 7 days post randomization between treatment arms. Secondary end points include all-cause mortality at 30 days, perihematomal edema volume after symptom onset, adverse events, vital signs, pharmacokinetics of MW189, and inflammatory cytokine concentrations in plasma (and cerebrospinal fluid if available). Other exploratory end points are functional outcomes collected on days 30, 90, and 180. BEACH will provide important information about the utility of targeting neuroinflammation in ICH and will inform the design of future larger trials of acute central nervous system injury.

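### The trial is sized on a 12% noninferiority limit but the primary decision rule applies 10%; under the planning assumptions power is then about 71%, not the stated 80%

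*Protocol article*

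**What the plan says.** All of the following is in the protocol article and concerns one quantity, the between-arm difference in 7-day all-cause mortality.

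- **Abstract:** 60 per group "will allow testing of the null hypothesis of noninferiority with a tolerance limit of 12" percent, assuming a "10% rate of death in each arm with 10% significance and 80% power".
- **Sample Size Determination:** "Considering a power of 80% and a one-sided 90% confidence interval", the aim is "to test the null hypothesis of noninferiority with a tolerance limit of 12" percent. With the same worst-case "safety assumption of 10% rate of death in each arm, the sample size per group was estimated to be 57", which is then raised to 60.
- **Statistical Analyses, primary outcome:** the difference in proportions is estimated "using a 90% one-sided confidence interval on the upper bound of this difference". Then comes the decision rule: "The null hypothesis will be rejected if this confidence interval is less than 10" percent.
- **Statistical Analyses, last sentence:** "Statistical significance will be set at" p < 0.05, with no statement of which analyses it covers.

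The confidence level and its sidedness agree in all three places. The limit does not.

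**The concern.** The primary safety conclusion has two thresholds. The sample size and the stated power belong to the wider one, and the written decision rule uses the narrower one. If the rule is followed as written, the trial has less power than it reports. If the limit is chosen once the data are known, the choice can decide the result and would be open to challenge, whichever way it went.

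Two matters of wording add to the uncertainty. The Abstract and the sample size section call noninferiority the null hypothesis, while the decision rule rejects the null when the upper bound is low. Read literally, a reassuring result rejects noninferiority. In addition, the unqualified p < 0.05 stands beside a primary test run at one-sided 10%.

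**Working it through.** **Inputs, all from the article.** Mortality 10% in each arm (true difference 0); one-sided alpha 10%, so z = 1.2816; power 80%, so z = 0.8416; 1:1 allocation; 57 per group calculated, 60 planned; limit m = 0.12 (Abstract, Sample Size Determination) or 0.10 (Statistical Analyses).

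**Step 1. Reproduce the stated sample size.** With the unpooled normal approximation,

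n per group = (1.2816 + 0.8416)² × 2 × 0.10 × 0.90 / m² = 4.508 × 0.18 / m²

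- m = 0.12: 0.8114 / 0.0144 = 56.3, rounded up to **57**, the article's figure.
- m = 0.10: 0.8114 / 0.0100 = 81.1, rounded up to **82**, or 164 in total before any allowance for withdrawal.

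The trial was therefore sized on 12%.

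**Step 2. Power under each limit.** Power = Φ(m / √(0.18/n) − 1.2816). At n = 60, √(0.18/60) = 0.05477.

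| Per group | Limit 12% | Limit 10% |
|---|---|---|
| 60 | Φ(2.191 − 1.282) = 81.8% | Φ(1.826 − 1.282) = 70.7% |
| 57 | 80.3% | 69.1% |

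**Step 3. Check against exact enumeration.** Summing the binomial probabilities over all outcomes at 60 per group and 10% mortality in each arm:

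- Wald upper bound: 82.1% at 12%, 71.9% at 10%.
- Farrington-Manning score test at the 10% limit: 68.7% (67.8% by its normal approximation).

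Every method puts the 10% rule at about 68% to 72%.

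**Step 4. Data on which the two limits disagree.** Placebo 6/60 deaths, Wald bound = difference + 1.2816 × SE:

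| MW189 deaths | Difference | SE | Upper bound | At 12% | At 10% |
|---|---|---|---|---|---|
| 7/60 | 1.7% | 5.67% | 8.9% | pass | pass |
| 8/60 | 3.3% | 5.85% | **10.8%** | **pass** | **fail** |
| 9/60 | 5.0% | 6.02% | 12.7% | fail | fail |

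Under the planning assumptions, the exact probability that the bound lies from 10% up to 12% is 10.2%.

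**Step 5. What the choice means for protection.** If true mortality were 20% on MW189 and 10% on placebo, exact enumeration of the Wald rule declares noninferiority in 10.8% of trials with the 10% limit and 17.2% with the 12% limit.

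**Step 6. The p < 0.05 sentence.** If it were taken to govern the primary test one-sided, power at 60 per group would be 70.7% at the 12% limit and 57.2% at the 10% limit. The article does not propose this test. The figures show only why the scope of the sentence should be stated.

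**The case against.** Nobody can reasonably dispute that the two limits differ. The arguments on the other side concern how much follows from it.

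- **The 10% may be a slip.** It is also the significance level and the assumed death rate, and two sections agree on 12%. If so, no power is lost. This is plausible, but the text does not show it, and the slip would sit in the decision rule itself. It still has to be corrected before unblinding.
- **The 71% is conditional.** The article calls 10% mortality a worst case and hopes for fewer deaths on MW189. Taking other rates as assumptions, power under the 10% rule at 60 per group is 77% with 8% mortality in both arms, 81% with 7% and 89% with 5%. With 8% on MW189 and 10% on placebo it is about 85%. This stands as a qualification, but the article's stated 80% rests on the 10% rate, so that is the right basis for comparison.
- **The stricter rule is the safer one.** True: following 10% as written costs power and does not loosen the conclusion. It does not remove the problem of two rules.
- **This is an exploratory phase 2a trial.** It is, but it has a formal primary hypothesis with a stated limit, level and power.
- **The reversed null and the p < 0.05 sentence are editorial.** Largely accepted. The intended direction of the test is clear from the aim in the Discussion, and p < 0.05 closes a paragraph on secondary and exploratory outcomes. Both are minor, and a clause each would settle them.
- **The full protocol or analysis plan may fix the limit.** It may. The article would still contradict itself and need correction.

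**Conclusion.** The concern holds. The article gives two limits for its one primary decision, and the stated sample size and power belong to 12% while the written rule uses 10%. If the rule governs, planning power at 60 per group is 70.7%. That is about 9 points below the stated 80% and 11 below the 81.8% that the 12% limit would give. This rests on the article's own assumptions: 10% mortality in both arms, 60 evaluable per group, one-sided alpha of 10% and the unpooled normal approximation. Other standard methods give about 68% to 72%. Under the same assumptions, about one trial in ten would have its primary conclusion settled by which sentence is followed. The documents do not show which limit was intended. The matter must be fixed before unblinding. The wording of the null and the scope of p < 0.05 are lesser points to correct at the same time.

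**What to change.** Fix one limit before unblinding and use it in the Abstract, Sample Size Determination and Statistical Analyses. There are two ways:

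1. Restate the decision rule so that noninferiority is concluded when the upper one-sided 90% limit for the difference is below 12%, the limit that sized the trial. Power at 60 per group is then 81.8%, and the stated 57 and 80% stand.
2. Keep 10% and restate power as about 70% in the Abstract and Sample Size Determination. Keeping 80% power with this limit would instead need 82 per group.

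In either case:

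- Write the null as H0: mortality on MW189 minus mortality on placebo ≥ the limit, rejected when the upper bound falls below it.
- State that p < 0.05 does not apply to the primary test.

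The cost is wording in the protocol and the analysis plan. Keeping 10% at the present size also means reporting a less favourable power. Neither numbered option, as restated, needs extra patients.

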### Patient Population

A total of 120 participants (60 per group) with acute spontaneous nontraumatic ICH are eligible for this study. The inclusion and exclusion criteria are detailed in Table 1. Written informed consent will be obtained from all participants or their legally authorized representatives.

**Table 1 Tab1:** Inclusion and exclusion criteria

Inclusion criteria: a patient will be eligible for inclusion in the study only if all of the following criteria are met:	
Confirmed diagnosis of spontaneous nontraumatic ICH	
10 mL ≤ ICH ≤ 60 mL (confirmed via diagnostic and stability CT scans using volumetric assessment)	
Participants receiving anticoagulants are eligible upon reversal and stability within 24 h after onset of ICH symptoms	
Age ≥ 18 years	
Able to receive first dose of test article (drug or placebo) ≤ 24 h after onset of ICH symptoms	
NIH Stroke Scale score ≥ 2 at randomization or Glasgow Coma Scale score ≥ 5 at randomization	
Controlled blood pressure (systolic blood pressure ≤ 160 mm Hg) at randomization	
Premorbid modified Rankin Scale score of 0–2	
Has adequate venous access	
No planned surgical intervention except external ventricular drain	
Written informed consent from the patient or legally authorized representative	
Exclusion criteria: a patient will not be eligible for inclusion in the study if any of the following criteria are met:	
Unstable hematoma defined as > 6-mL increase as compared to previous CT volume taken at least 6 h apart within 24 h after onset of ICH symptoms	
Anticipated neurosurgical evacuation by open surgery or minimally invasive surgery with or without alteplase (external ventricular drain allowed)	
Uncontrolled temperature > 38.5 °C at enrollment	
Signs of intracranial infection or emergence of a systemic infection	
Is pregnant or lactating	
Signs of liver and kidney chronic disease (i.e., creatinine > 2 mg/dL, bilirubin ≥ 3 mg/dL, receiving dialysis)	
Nonreversible bleeding diathesis	
Used any chronic immunosuppressants or chronic antiinflammatory drugs (excluding low-dose aspirin) by any route of administration within the past 7 days	
Anticipated withdrawal of life-sustaining therapies within the first week after admission	
In the opinion of the investigator, patient has any contraindication to the planned study assessments	

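### The supplementary adjusted model for 7-day mortality conditions on withdrawal of life-sustaining therapy, a post-randomization event on the path to death, with only about 12 deaths expected

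*Protocol article*

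**What the plan says.** All of this is in the Protocol article.

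- **Primary analysis (Statistical Analyses).** The decision uses a one-sided 90% upper confidence bound for the difference in 7-day mortality. No covariates are named for it.
- **Supplementary model (Statistical Analyses).** A multivariable logistic regression of 7-day mortality is then added. Its covariate list begins "This model will consider age, sex, race and ethnicity, ICH volume at stability" and continues with GCS score, IVH, withdrawal of life-sustaining therapy, and deep or lobar location.
- **Timing of the covariates (same section).** Age, sex, and race and ethnicity come from screening, GCS from baseline, IVH and location from the diagnostic CT, and ICH volume from the stability CT. Withdrawal is the exception: "Withdrawal of life-sustaining therapy information is collected at any time during the study period".
- **Eligibility (Table 1).** One exclusion criterion is "Anticipated withdrawal of life-sustaining therapies within the first week after admission".
- **Planning rate (Sample Size Determination).** The plan makes a worst-case "safety assumption of 10% rate of death in each arm" and concludes that "120 participants (60 per group) are required to evaluate the safety of MW189".
- **Other safety models (end of Statistical Analyses).** The covariate list for secondary and exploratory safety outcomes does not include withdrawal.

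**The concern.** A covariate in a model for the effect of randomized treatment should be fixed before treatment can influence it. Withdrawal of life-sustaining therapy is not. Patients in whom it is anticipated are kept out, so what is recorded is essentially a decision made after randomization. That decision may follow from deterioration, and it is closely tied to death.

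Suppose MW189 worsened some patients so that care was withdrawn and they died. Comparing arms within levels of withdrawal would then take that pathway out of the treatment coefficient. In a first-in-patient trial whose aim is to show no increase in early mortality, this error is in the unsafe direction: an excess of deaths could be reported beside an adjusted odds ratio near 1.

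The second problem is practical. A covariate that nearly determines the outcome, in a model with many terms and few deaths, invites separation. The maximum-likelihood estimate is then not finite and the analysis may not be available.

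**Working it through.** **1. The plan's own figure.** Inputs from Sample Size Determination: 10% mortality in each arm, margin 12 points, one-sided alpha 0.10, power 80%.

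n = (z0.90 + z0.80)² × [p(1−p) + p(1−p)] / margin² = (1.2816 + 0.8416)² × 0.18 / 0.0144 = 4.508 × 12.5 = 56.4, so 57 per group. This agrees with "the sample size per group was estimated to be 57", and confirms 10% as the working death rate.

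**2. Deaths per slope.** Expected deaths = 120 × 0.10 = 12 (binomial 95% range 6 to 19). Treatment plus eight covariates is 9 slopes if race and ethnicity is one binary term, and 11 with three indicators.

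- 12 / 9 = 1.33 deaths per slope; 12 / 11 = 1.09.
- At 20% mortality, 24 / 9 = 2.67.
- With withdrawal removed, 12 / 8 = 1.5.

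**3. Masking, by hand (assumed rates, not in the article).** Let withdrawal occur in 8% on placebo and 18% on MW189. Let 7-day death follow in 95% of those withdrawn and 2% of the others, in both arms.

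- Placebo: 0.08 × 0.95 + 0.92 × 0.02 = 9.44%.
- MW189: 0.18 × 0.95 + 0.82 × 0.02 = 18.74%.
- Difference: 9.3 points. Odds ratio: (0.1874/0.8126) / (0.0944/0.9056) = 2.2.
- Within each level of withdrawal the arms have equal risk, so the withdrawal-adjusted odds ratio is 1.0.

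**4. Masking and failure, by simulation.** Assumed prognostic effects for age, ICH volume, GCS and IVH; withdrawal depends on these and on treatment; death depends only on withdrawal. There were 500 trials of 120 per setting, plus one large sample for the limiting odds ratio. Failure means non-convergence or a diverging coefficient. Failure rates are at 10% against 10% mortality; odds ratios are at 22% against 10%.

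| Death risk with / without withdrawal | OR, withdrawal omitted | OR, withdrawal included | Failure, omitted (7 slopes, no race) | Failure, included (8 slopes, no race) | Failure, included (11 slopes, 3 race terms) |
|---|---|---|---|---|---|
| 70% / 5% | 2.64 | 1.01 | 3% | 16% | 62% |
| 80% / 3% | 2.70 | 0.98 | 3% | 37% | 76% |
| 90% / 2% | 2.71 | 1.01 | 3% | 72% | 90% |
| 100% / 3% | 2.68 | not estimable | 4% | 100% | 100% |

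With more deaths (22% against 10%), failure of the 8-slope model falls to 5%, 17% and 57% in the first three rows, and stays at 100% in the last.

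**5. Does the primary test miss the harm in step 3?** SE = √[(0.0944 × 0.9056 + 0.1874 × 0.8126) / 60] = √(0.2378 / 60) = 6.3 points. The expected upper bound is 9.3 + 1.28 × 6.3 = 17.4 points. The article gives a 12-point margin for sample size and 10 points in the decision rule, a separate matter, so both are shown. By normal approximation, noninferiority would be declared in about 12% of such trials at 10 points and about 20% at 12 points.

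**The case against.** **The model does not decide the trial.** A reader might infer that MW189 could be declared safe because this model hides harm. The article does not support that. The decision rests on the confidence bound for the difference in proportions, the model is an addition to it, and nothing lets the adjusted odds ratio override the bound. The safety board's review is not tied to the model either. Step 5 shows that the primary test would usually fail to declare noninferiority in the illustrated case. This objection stands and limits the point to a supporting estimate.

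**The sizes are assumed.** The article gives no withdrawal rates, no death risk after withdrawal and no share of harm acting through it. An odds ratio of 1.0 follows from letting all of the harm act through withdrawal; partial mediation would mask only part. Excluding anticipated withdrawal should also lower first-week rates. This too stands.

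**Late withdrawals.** A reader might infer that withdrawals after day 7 enter a model of 7-day death. The sentence describes when information is collected and does not define the covariate, so this is an ambiguity to close, not an established error.

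**The long covariate list.** A reader might conclude that the list alone makes the model unusable. Without withdrawal, and with race also left out, failure was only 3 to 4%. Much of the instability therefore comes from withdrawal, although the race terms add to it. Race coding and any penalized fit may properly be left to an analysis plan, and the verb in "This model will consider age, sex, race and ethnicity, ICH volume at stability" is somewhat soft.

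**Withdrawal is strongly prognostic, and practice may vary.** That is a reason to report it. It does not make it a valid covariate for the total effect of treatment on death.

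**Conclusion.** The point holds for the supplementary model. The article names a post-randomization event on the path to death as a covariate, and nothing else in it corrects this. The direction of the problem follows from the design: harm acting through withdrawal is removed from the adjusted estimate, in part or in full.

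Its size is conditional. With full mediation and the assumed rates, a true odds ratio of about 2.6 to 2.7 becomes about 1.0; with no effect of treatment on withdrawal, this masking would not arise. Sparse data follow from the plan's own figures, at most 1.33 deaths per slope at the planning rate. Failure of the fit ranges from 16% to 100%, depending on death risk after withdrawal and on race coding.

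The noninferiority decision is untouched. What is compromised is the only named adjusted estimate of the primary safety outcome. This should be corrected, but it does not undermine the trial's primary conclusion.

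**What to change.** Delete withdrawal of life-sustaining therapy from the logistic model for 7-day mortality and adjust only for covariates fixed before randomization. Report withdrawal descriptively by arm as a post-randomization outcome, with its timing relative to day 7.

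Optional, as a matter of judgment given about 12 deaths:

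- prespecify a shorter list of baseline covariates, or use a Firth penalized fit;
- standardize the model's predictions to an adjusted risk difference, since the article says the model is to estimate a difference in proportions.

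The cost is wording in the protocol and the analysis plan; no new data or participants are needed. The small downside is that fewer covariates are adjusted for. The change should be made before unblinding, because dropping a covariate later would look data-driven.
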